**S2: Study Protocol v4 (13.09.2021)**

Study questions

*1. If practicing yoga, learning the Bhagavad Gita, or combining both reduces psychological distress, then participants in these intervention groups will show significant reductions in GAD7 scores over time compared to their baseline scores.*

*2. If the interventions are more effective than no intervention, then the GAD7 scores will be significantly lower in the intervention groups compared to the control group at post-intervention assessments.*

*3. If learning the Bhagavad Gita results in more lasting stress reduction than practicing yoga alone, then the Gita group will have lower GAD7 scores at the delayed post-intervention assessment than the Yoga group.*

*4. If combining yoga and the Bhagavad Gita has a synergistic effect, then the Yoga+Gita group will experience greater immediate and sustained reductions in GAD7 scores than either intervention alone.*

*5. If no significant changes occur in the control group over time, then the GAD7 scores in the control group will remain relatively stable across all assessments.*

*6. If the interventions differ in their sustained effectiveness, then the Gita and Yoga+Gita groups will have significantly lower DPI-GAD7 scores compared to the Yoga group at 45 days post-intervention.*

*7. Gender may moderate the effect of the interventions on psychological distress.*

*8. Educational attainment may moderate the effect of the interventions on psychological distress.*

*9. If continued practice of the interventions is important for sustained stress reduction, then participants who continue practicing the interventions will have lower GAD7 scores at the delayed post-intervention assessment than those who do not continue.*

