**Analysis Plan**

Statistical models

*Descriptive Statistics:* Before any inferential tests, we will compute descriptive statistics (mean ± standard deviation for continuous variables and frequencies/percentages for categorical variables) to describe the demographic characteristics (age, gender, education level) and baseline GAD7 scores for each group.

*Tests for Normality:* To determine the appropriate statistical tests, we will first assess the normality of the GAD7 scores using the Shapiro-Wilk test. If the data are normally distributed, we will proceed with parametric tests. If the data do not meet normality assumptions, we will use non-parametric alternatives.

*Primary Plan (Parametric Tests):*

Within-Group Comparisons: To examine changes in GAD7 scores over time (Baseline, Immediate Post-Intervention, and Delayed Post-Intervention) within each group, we will use repeated-measures ANOVA. If significant, we will conduct pairwise t-tests with Bonferroni correction to compare GAD7 scores between each pair of time points (e.g., Baseline vs. IPI-GAD7, Baseline vs. DPI-GAD7).

Across-Group Comparisons: To compare GAD7 scores between the four groups (Control, Yoga, Gita, Yoga+Gita) at each time point (Baseline, IPI-GAD7, DPI-GAD7), we will use one-way ANOVA. If significant differences are found, we will apply Tukey’s HSD for post-hoc pairwise comparisons between groups.

Subgroup Analysis (by Gender, Educational Attainment, and Continued Practice): For subgroup analyses, we will use two-way ANOVA to assess whether gender (male, female), education level (Bachelor’s vs. Master’s or higher), and continued practice (yes, no) influence GAD7 score changes over time or interact with the interventions.

Effect Size Calculations: Partial eta-squared (η²) will be calculated for repeated measures ANOVA and η² will be calculated for one-way ANOVA to estimate the effect sizes.

*Backup Plan (Non-Parametric Tests):*

Within-Group Comparisons: We will use the Friedman Test to compare GAD7 scores over time within each group (Baseline, IPI-GAD7, DPI-GAD7). If significant, we will perform pairwise comparisons using the Conover Test to identify specific differences between time points.

Across-Group Comparisons: To compare GAD7 scores across the four groups at each time point, we will use the Kruskal-Wallis Test. If significant, we will conduct the Dunn’s Test for pairwise group comparisons.

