Subgroup Analysis (by Gender, Educational Attainment, and Continued Practice): For the gender, education, and continued practice subgroup analyses, we will use the Mann-Whitney U Test to compare GAD7 scores between subgroups at each time point.

Effect Size Calculations: We will compute the Kendall’s W for effect size in the Friedman test and η² for the Kruskal-Wallis test to estimate the effect sizes. Statistical Significance: For all tests, a two-tailed p-value < 0.05 will be considered statistically significant.

Transformations

*None*

Data exclusion

*Participants who miss any follow-up session (B-GAD7, IPI-GAD7, DPI-GAD7) will be excluded.*

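### On the non-parametric backup route, the gender and education moderation questions (7 and 8) get only a Mann-Whitney test between subgroups, which contains no test of moderation

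*Protocol*

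**What the plan says.** Question 7 in the Protocol's list of study questions reads "Gender may moderate the effect of the interventions on psychological distress", and question 8 reads "Educational attainment may moderate the effect of the interventions on psychological distress". Both concern moderation, that is, whether the difference between arms depends on the subgroup.

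The Analysis Plan has two routes. Under Tests for Normality, "we will first assess the normality of the GAD7 scores using the Shapiro-Wilk test"; then, "If the data do not meet normality assumptions, we will use non-parametric alternatives". On the parametric route the subgroup item says "we will use two-way ANOVA to assess whether gender (male, female), education level" and continued practice "influence GAD7 score changes over time or interact with the interventions". On the backup route the subgroup item for the same three factors says "we will use the Mann-Whitney U Test to compare GAD7 scores between subgroups at each time point". No other non-parametric method for moderation is given, and Transformations is answered with None. The significance rule is common to both routes: "For all tests, a two-tailed p-value < 0.05 will be considered statistically significant".

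**The concern.** The two routes share a subgroup heading but answer different questions. A two-way ANOVA with an interaction term asks whether the intervention effect differs between men and women. A Mann-Whitney test between men and women asks whether their GAD7 scores differ, and arm does not enter. Once the backup applies, two of the nine study questions have no analysis that addresses them.

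Two errors then become possible. An ordinary gender or education difference, with no bearing on the interventions, can give a significant result under the heading meant for questions 7 and 8. Real moderation can go unseen. A statistical analysis plan would not simply be filling a gap here, because the protocol itself names the test.

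**Working it through.** **1. The contrasts.** Let m(k,s) be mean GAD7 in arm k (control and three interventions) and sex s.
- Moderation: [m(k,F) − m(control,F)] − [m(k,M) − m(control,M)] differs from 0 for some intervention k.
- Pooled Mann-Whitney, with equal numbers in each cell: in essence, the average of m(k,F) over arms against the average of m(k,M). It can be far from zero with no moderation, and zero with strong moderation.
- Mann-Whitney within arm k: m(k,F) against m(k,M). No arm is compared with control, so this is not the moderation contrast either.

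**2. Inputs.** From the Protocol, Sample size: difference 4, SD 3.78, power 80%, alpha 0.05. No sample size is stated, so there is no figure to reproduce. For two groups, n = 2(1.96 + 0.84)² × 3.78² / 4² ≈ 14.0, so 15 per arm, or 16 with the t distribution. Assumed: 16 completers per arm, a 50:50 gender split, normal scores, one post-intervention time point, and an effect of −4 in each intervention unless stated otherwise.

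**3. Hand check, no moderation.** There are 32 men and 32 women. Arm effects 0, −4, −4, −4 add variance 16 × 0.25 × 0.75 = 3, so the SD over arms is √(3.78² + 3) = √17.29 = 4.16. The critical difference in means is about 1.96 × 4.16 × √(2/32) = 2.04. Because the sexes are balanced within arms, the actual standard error of the difference is 3.78 × √(2/32) = 0.945. Rejection is about Φ((2 − 2.04)/0.945) = 48% for a 2-point gender gap and Φ((3 − 2.04)/0.945) = 85% for 3 points. This approximates a comparison of means; the rank test comes out slightly lower.

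**4. Simulation, 3,000 trials per setting, 16 per arm.** Rejection at 0.05:

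| Truth | Pooled Mann-Whitney | Within arm, at least one of four | Arm-by-gender F test |
|---|---|---|---|
| No moderation, no gender gap | 3% | 19% | 5% |
| No moderation, gap of 2 | 44% | 51% | 6% |
| No moderation, gap of 3 | 81% | 76% | 6% |
| All interventions work in men only; women 3 lower | 4% | 47% | 29% |
| Yoga works in men only, Gita in women only, combination in both | 2% | 75% | 68% |

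In the last two rows the overall means cancel. Men average (0 − 4 − 4 − 4)/4 = −3 and women −3; then men average (0 − 4 + 0 − 4)/4 = −2 and women (0 + 0 − 4 − 4)/4 = −2. At 20 and 24 per arm the pattern is the same: the pooled test rises to 64% (gap 2) and 94% (gap 3) with no moderation, while the F test stays near 5%. The within-arm version rejects somewhere in 17-19% of trials with neither a gap nor moderation, and in 51-60% with a 2-point gap and no moderation.

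**5. How often the backup applies.** The protocol gives neither the score distribution nor the unit or level of the Shapiro-Wilk test. Assume level 0.05, any rejection triggers the backup, tests independent, rounded scores limited to 0-21, and SD 3.78:
- One test per time point over all arms (60 scores), normal shape, mean 8-10: 8.4-9.4% per test, so 1 − 0.916³ = 23% to 1 − 0.906³ = 26% over three tests.
- Twelve arm-by-time cells, mean 8-10, 15-25 per cell: 49-56%. Exactly normal data already give 1 − 0.95¹² = 46%.
- Strong floor effect, mean 4 in every cell: 22.4% per cell at 15 per cell, so 1 − 0.776¹² = 95%; 99% at 18 per cell.

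**The case against.** The strongest reply has four parts.

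*The protocol does not say the test is pooled over arms.* True, although the within-group and across-group items refer to the groups and this one does not. The within-arm reading does not rescue the plan (step 4).

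*The test is run at each time point, baseline included, so a reader could see a gap that was already there.* This is fair, and it means the tests are not wholly uninformative. If women gained 4 points more from every intervention with no earlier gap, the overall difference would be 4 × 3/4 = 3 points and the test would usually reject. But setting one p-value beside another is not a test of a difference in effect, and a change in the overall gap still does not show that it depends on arm. Nor does the protocol say that such a result would be called moderation; that is a risk, not a stated intention.

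*Questions 7 and 8 are secondary and tentatively worded, and the arm comparisons are untouched.* That limits the consequence but does not make the named test fit its question.

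*Stronger criticisms go beyond the text.* A reader might infer that the normality check will force the backup in most trials. The documents do not support this: the highest rates need a mean near 4 in every cell, including baseline, and no mean is given. A reader might also infer that the two-way ANOVA treats one person's repeated scores as independent. The text does not say so; a two-way ANOVA on change scores, or at one time point, uses one value per person. Finally, the defect gives no ground for replacing the analysis of every study question.

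**Conclusion.** The point holds for the backup route and for questions 7 and 8. The Mann-Whitney subgroup test cannot answer them on either reading, while the parametric route can. This follows from the form of the test and does not depend on any simulation.

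The size is illustrative: about 45% and 80% rejection for plain gender differences of 2 and 3 points, and about 3-5% or less when moderation cancels in the overall means. It rests on 16 per arm, SD 3.78, an even split and the pooled reading. The chance of reaching the backup is uncertain, from roughly 25% through 50% to near 100%, depending on facts the protocol does not state. Question 9 is not affected: it compares those who continue practising with those who do not, which a Mann-Whitney test can address. The change should be made, since following the stated rule leaves two stated questions unanswered.

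**What to change.** In the backup subgroup item, state that for questions 7 and 8 the arm-by-gender and arm-by-education interactions will be tested whatever the Shapiro-Wilk result. Suitable choices are a linear model for GAD7 with baseline, arm, subgroup and arm-by-subgroup terms and robust or bootstrap intervals, or a proportional-odds model with the same interaction. Name one in advance. Report the arm differences within each subgroup with confidence intervals and label these analyses exploratory. State that the Mann-Whitney subgroup tests are not evidence on moderation; they may stay for question 9.

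The cost is wording only: GAD7, arm, gender and education are already collected, and no more participants are needed. The drawback is low power, about 25-30% at 16 per arm for a 4-point difference in effect between subgroups, so a non-significant interaction should not be read as absence of moderation.

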**Design Plan**

Study type

*Experiment - Randomized controlled trial.*

Blinding

*Personnel who analyze the data collected from the study will not be aware of the treatment applied to any given group.*

Is there any additional blinding in this study?

*The researchers will be divided into three teams; each team will have no contact with the others once recruitment begins until data analysis is complete. The participant recruitment will be conducted by Team 1. Team 2 will coordinate with external volunteers and ensure that the interventions are administered smoothly; they will also collect the data. Team 3 will analyze the collected data; they will have no contact with the participants.*

Study design

*This study will use a between-subjects design with four levels (Control, Yoga, Gita, Yoga+Gita), incorporating repeated measures of psychological distress at three time points to assess both immediate and long-term effects of the interventions. Randomization will ensure equal distribution across groups, and no counterbalancing is expected to be needed.*

Randomization

*The study will use simple randomization via a chit-pull system at the individual participant level, ensuring equal and unbiased assignment to one of the four study groups. There will be no additional stratifications or blocks. The chits will be placed in a glass bowl, folded, with no visible marks to enable identification of their contents. Each participant will remove one chit from the bowl, and the chit will contain the participant IDs and the group assignments.*

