**Sampling Plan**

Existing Data

*None*

Data collection procedures

*Population:* The participants will be healthcare workers (HCWs) employed at Sri Jagannath Heath Care and Research Centre, Dhanbad, Jharkhand, India. They are facing significant psychological stress during this COVID-19 pandemic, making them suitable candidates for the study aimed at assessing interventions for stress reduction.

*Recruitment:* Participants will be recruited by posting a call for participation on the internal email system and notice board of the hospital. This announcement will include all relevant information about the study, such as the nature of the interventions, expected commitment, and the informed consent form. No payments will be provided for participation.

*Inclusion and Exclusion Criteria:*

Inclusion Criteria: Participants will be aged 18 years or over and be currently employed HCWs at the hospital. They will also need to be available for the entire duration of the intervention (1 week) and follow-up (45 days post-intervention).

Exclusion Criteria: Participants with pre-existing diagnosed mental health conditions will be excluded to ensure that the study focuses on measuring the effect of the interventions on psychological distress caused by work-related stress during the pandemic, rather than on pre-existing disorders.

*Grouping:* After the eligible HCWs return the signed informed consent forms, they will be randomized into one of four groups (Control, Yoga, Gita, Yoga+Gita) using a chit-pull system, as previously described, in a 1:1:1:1 ratio.

*Study Timeline:* Recruitment will begin on October 25, 2021, and end on November 5, 2021. The baseline assessment (B-GAD7) will be administered on November 12, 2021. The interventions (Yoga, Gita, Yoga+Gita) will be conducted between November 13, 2021, and November 19, 2021. The immediate post-intervention GAD7 (IPI-GAD7) will be collected on November 20, 2021 (1 day post-intervention). The delayed post-intervention GAD7 (DPI-GAD7) will be administered on January 3, 2022 (45 days post-intervention).

*Intervention Details:* Participants in the intervention groups will attend daily 1-hour sessions for one week. The Yoga group will practice yoga for the entire hour. The Gita group will attend Bhagavad Gita lessons for one hour. The Yoga+Gita group will have 30 minutes of yoga followed by 30 minutes of Bhagavad Gita lessons. The Control group will not receive any intervention.

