*Data Collection Process:* Psychological distress will be measured using the Generalized Anxiety Disorder-7 (GAD7) scale at three time points; Baseline (B-GAD7) - Administered before the interventions starts, Immediate Post-Intervention (IPI-GAD7) - Administered 1 day after the last intervention session, and Delayed Post-Intervention (DPI-GAD7) - Administered 45 days after the intervention. All data will be collected anonymously using only the participant identification numbers (PINs) to maintain confidentiality.

*Data Management:* The consent forms and a document linking participants’ names to their PINs will be securely stored and not accessible to the data analysis team or to the intervention coordination and data collection team. The data will include GAD7 scores and demographic information (age, gender, education level).

Sample size

*The sample size will be calculated to detect significant effects with 80% power to detect a minimum clinically important difference of 4 for the GAD7 with a standard deviation of 3.78 at the standard alpha error of 0.05. A dropout rate of 15% will be considered. PASS 2020, v20.0.6 will be used to calculate the sample size.*

Stopping rule

*None*

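### The exclusion rule drops a participant from every analysis for one missed GAD7, so it discards immediate post-intervention scores that the between-group test could use; it also biases that comparison if loss depends on outcome differently by arm

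*Protocol*

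**What the plan says.** Under Analysis Plan, Data exclusion, the protocol states: "Participants who miss any follow-up session (B-GAD7, IPI-GAD7, DPI-GAD7) will be excluded". Nothing limits this to particular analyses. The protocol describes no analysis set based on all randomised participants, no missing-data method and no sensitivity analysis.

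The statistical models in the same section are of two kinds. For change over time the plan is: "within each group, we will use repeated-measures ANOVA", with the Friedman test as backup. For differences between the four groups it is a one-way ANOVA, or Kruskal-Wallis as backup, run separately at baseline, IPI and DPI.

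Loss is expected. The sample size paragraph in the Sampling Plan says: "A dropout rate of 15% will be considered".

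On timing, the Sampling Plan says: "After the eligible HCWs return the signed informed consent forms, they will be randomized into one of four groups". It adds "Recruitment will begin on October 25, 2021, and end on November 5, 2021" and "The baseline assessment (B-GAD7) will be administered on November 12, 2021". Under Randomization in the Design Plan, "the chit will contain the participant IDs and the group assignments", and GAD7 data are later collected under that identifier.

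**The concern.** IPI and DPI both come after allocation, so the rule removes people from the randomised groups because of something that happens later. A participant who attends the whole week and gives an IPI score, then misses the January assessment, disappears from the IPI comparison as well. That comparison bears directly on study question 2 (intervention against control after the intervention).

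Two things are at stake. The first is precision at IPI, lost although the data exist. The second is comparability of the groups. Three arms attend daily one-hour sessions for a week and the control arm receives nothing, and the participants are working hospital staff described as under significant stress. Attendance at a later assessment could therefore depend both on arm and on how the person feels. If it does, those who remain are a selected subset, selected differently in different arms. The 15% allowance protects power; it does nothing for comparability.

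**Working it through.** **1. Which planned tests need complete cases?**

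| Planned analysis | Scores needed per person |
|---|---|
| Within-group repeated-measures ANOVA or Friedman | All three |
| Between-group one-way ANOVA or Kruskal-Wallis at IPI | IPI only |
| Between-group one-way ANOVA or Kruskal-Wallis at DPI | DPI only |

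For the between-group tests, the rule's own added loss is the IPI scores of people who missed DPI or baseline, and the DPI scores of people who missed IPI or baseline. Someone who missed DPI has no DPI score, so the planned DPI test would lose that person even without the rule.

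**2. How many people?** The protocol states no sample size. From its inputs (difference 4, SD 3.78, two-sided alpha 0.05, power 80%, dropout 15%) there are two possible readings, both assumed:

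- Two-group formula: n = 2 × (1.960 + 0.842)² × 3.78² / 4² = 14.02, so 15 per arm. 15 / 0.85 = 17.6, so 18 per arm.
- Four-group ANOVA, extreme means 4 apart and the other two midway: f = √[(4 + 0 + 0 + 4)/4] / 3.78 = 0.374. Total 82, so 21 per arm. 21 / 0.85 = 24.7, so 25 per arm.

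At 15% loss the rule removes 0.15 × 18 = 2.7 to 0.15 × 25 = 3.75 people per arm, about 3 to 4.

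**3. Precision.** If 15% miss only DPI, the standard error of the IPI difference grows by a factor of 1/√0.85 = 1.08, about 8%, whatever the reason for the loss.

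**4. Bias, by large-sample simulation.** From the protocol: SD 3.78 and 15% loss. Assumed: all loss is at DPI only; between-visit correlation 0.6; random loss in control; in the intervention arm the log-odds of loss rise linearly with the IPI score. The true difference is 0. Entries are completers-only differences (control minus intervention), so positive values are spurious benefit.

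| Log-odds per SD | IPI | DPI |
|---|---|---|
| 0 | about 0 | about 0 |
| 0.5 | 0.27 | 0.17 |
| 1.0 | 0.50 | 0.29 |
| 1.5 | 0.66 | 0.39 |

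Using every observed IPI score gives an IPI difference of about 0 throughout, because under these assumptions nobody's IPI score is missing. The DPI column is bias from missing data in general, not from this sentence alone (step 1).

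**5. Same mechanism in both arms.** With no true effect the two shifts cancel and the net IPI bias is about 0. With a true 4-point effect, log-odds 1 to 1.5 and the 15% loss set in the control arm, the IPI difference is reduced by 0.28 to 0.44 points, towards no effect.

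**6. Scale.** 0.27/4 = 7% and 0.66/4 = 17% of the 4-point difference. With 15 completers per arm, the standard error of a pairwise difference is 3.78 × √(2/15) = 1.38, so a shift of 0.27 to 0.66 is about 0.2 to 0.5 standard errors.

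**The case against.** The strongest defence is that the rule has a reason. Repeated-measures ANOVA and Friedman need all three scores, and one common set keeps the IPI and DPI results on the same people, which helps when immediate and sustained effects are set side by side. Eligibility also requires availability through the 45-day follow-up, which should limit loss. The illustrated bias is well under one standard error and rests on assumptions outside the protocol.

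Much of this stands. It justifies complete cases for the within-group tests and tempers the rating. It does not justify discarding IPI scores from a between-group test that needs only IPI, and the availability criterion does not remove the loss that the protocol itself allows for.

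A reader might infer more than the document supports in three ways:

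- *That the rule necessarily breaks the randomised comparison.* Bias needs missingness related to outcome with an effect that differs by arm. The protocol contains no evidence on who misses assessments.
- *That all bias from loss at DPI is due to this sentence.* Most of it would remain under the planned DPI test if the sentence were deleted.
- *That a missed baseline is certainly a post-randomisation exclusion.* The order of consent, chit and identifier, and the baseline date a week after recruitment closes, suggest it, but no randomisation date is stated.

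**Conclusion.** The point holds in a limited form. The protocol fixes an unqualified complete-case rule that discards observed, usable scores of randomised participants, chiefly at IPI. This is a stated choice, not a detail left for an analysis plan to supply. Whenever someone misses only some assessments, precision is lost. Whether there is also bias, and in which direction, depends on a dropout mechanism that the document does not describe. Under one-arm, score-dependent loss of 15%, correlation 0.6 and log-odds 0.5 to 1.5 per SD, the spurious IPI difference is about 0.3 to 0.7 points. Under unrelated loss, or equal mechanisms with no true effect, it is about 0. As no alternative analysis is planned, the trial could not tell these cases apart. Severity: should-fix.

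**What to change.** Replace the data exclusion sentence with: *Participants are analysed in the group they were randomised to, and every available GAD7 score is used; no participant is excluded from a time point because another assessment was missed.*

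Then align the analyses:

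- Make the between-group comparison at IPI and DPI a mixed model for repeated measures on all available scores. Enter baseline as one of the outcome time points, not as a covariate: a covariate model in its standard form drops anyone without a baseline score.
- If the non-parametric backup is used, apply Kruskal-Wallis to all scores available at each visit.
- Keep the complete-case analysis as a sensitivity analysis, and add one delta-shift analysis for missing DPI scores, because the mixed model assumes data are missing at random.

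The replacement sentence alone would recover the discarded scores for the planned per-visit tests. The mixed model goes further by using earlier scores to inform missing DPI values. Someone with no GAD7 score at all still contributes nothing and should be reported by arm.

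The cost is a change of wording and slightly more analysis, with no extra participants or visits. The one real downside is that IPI and DPI results will rest on slightly different sets of observed people.
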